## 4.6 Schedule

Expected total study duration: 44 months

Milestones (month/year):

| Preparations/planning | 05/2020 |
| --- | --- |
| Inclusion of first patient | 08/2020 |
| Inclusion of last patient | 05/2021 |
| Inclusion of first volunteer | 08/2020 |
| Inclusion of last patient | 07/2021 |
| End of statistical analysis | 12/2022 |
| Final report | 12/2023 |

# 5 Selection

## 5.1 Inclusion criteria

**Patients n=60**

- facial nerve palsy diagnosed by a doctor
- all ages
- written informed consent from patient or legal guardian (for patients under 18 years of age) to participate in study
- toothed
- not suffering from any of following diagnosed diseases: Haemophilia A and B, Epilepsy, Aids

**Controls n=60**

- selection with regard to age and sex as a control group to previously examined patients
- no facial nerve palsy ever diagnosed
- written consent of the subject or legal guardian (for subjects under 18 years of age) to participate in the study
- toothed
- not suffering from any of the following diagnosed diseases: Haemophilia A and B, Epilepsy, Aids

## 5.2 Exclusion criteria

**Patients**

- multimorbid patients
- no diagnosed facial nerve palsy
- lack of consent from patient or legal guardian (for patients under 18 years of age) to participate in study
- edentulous
- suffering from one of following diagnosed diseases: Haemophilia A and B, Epilepsy, Aids

**Controls**

- multimorbid subjects
- age and gender mismatch with previously studied patients
- diagnosed facial nerve palsy currently or in past
- lack of consent from control or legal guardian (for subjects under 18 years of age) to participate in study
- edentulous
- suffering from one of following diagnosed diseases: Haemophilia A and B, Epilepsy, Aids

# 6 Procedure of the study

## 6.1 Information and consent

At beginning of study, persons (from patient or control group) will be given an information sheet (see appendix), which provides information about nature of the study, objectives, procedure, duration, benefits, possible risks, data evaluation, data protection and participant rights, as well as a consent form (see appendix). After reading both forms thoroughly, the examiner ensures that the patient/control person has understood the information and gives him/her the opportunity to address any open questions and have them answered in detail. Persons have sufficient time to decide whether to participate in the study. In next step, participant will be asked, if he or she is interested in the study, to document his or her knowledge and consent in writing. This consent also explicitly refers to collection and processing of personal data. Based on this, patients/controls will be informed in detail and explicitly about purpose and scope of collection and use of this data.

Patients/controls will subsequently receive a copy of signed consent form, original will remain with the examiner. Participants can withdraw this consent at any time without giving reasons and without detriment to his/her further treatment, discontinue the study and withdraw from the study. In this case, time of discontinuation of participation will be documented. If the consent form is not signed, subject will not be included in study.

Only when the person has affirmatively signed both forms, the person has been given an appropriate copy of documents and all other questions have been clarified, study will begin.

## 6.2 Questionnaire

Prior to examination of persons, a questionnaire (Questionnaire 1, subjective assessment of own oral hygiene and oral health, see Appendix) will be handed out to participants and discussed with the patient/control person in interview. In case patient/control person prefers to complete questionnaire alone, he/she will be allowed to do so. Patients/controls are asked to complete questionnaire as truthfully and intuitively as possible.

Questionnaire collects important information such as person's attitude towards his/her own oral hygiene, previous performance of dental cleaning as well as possible risk factors for development of poorer oral hygiene in order to determine whether occurring deficits in oral hygiene already existed before facial nerve palsy or whether the person may also have genetic or motor-related limitations, whereby poorer oral hygiene could no longer be directly attributed to facial nerve palsy. Questionnaire should therefore provide the examiner the opportunity to get to know the patient/control person better with regard to his/her oral hygiene and to be able to assess him/her more successfully with regard to this.

## 6.3 Oral examination

Oral examination of patients follows the same procedure as that of controls.

During oral examination, the examiner inspects the well-lit oral cavity and diagnoses teeth, gingiva and oral mucosa as well as existing dentures as oral structures. A complete dental status of the person including tooth restorations and their tooth mobility, periodontal health by means of PSI, presence of calculus, MPD as well as attachment loss, gingival bleeding by means of mod. SBI according to Lange et. al 1986 and PBI according to Mühlemann and Saxer 1975, caries infestation using PUFA index according to Monse et al. 2010 and caries activity, plaque infestation using API according to Lange et al. 1986 and TI according to Turesky et al. 1970, abnormalities in oral mucosa according to WHO classification and presence of halitosis were examined and documented. A paper-based report form (see appendix) is used to record and document the dental status and various oral health parameters, which is converted into an Excel document later. After findings have been recorded, intraoral photographs are taken.

If desired, patients can ask the examiner open questions regarding oral care and receive expert advice for optimal tooth cleaning and plaque management.

Examinations are carried out on premises of ENT department at Jena University Hospital. An examination of controls is also conceivable in a dental practice. Participating patients and controls will be examined and treated in a standardized manner in the ENT-clinic of Jena University Hospital with regard to their illness independently of the planned study. Data obtained on oral health of patients/controls will be communicated to them and treated confidentially, but will have no influence on further dental and ENT treatment of patients.

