## 4.3 Type of comparison group

A corresponding control group of volunteers not suffering from facial nerve palsy will be recruited in exactly the same way as the patient group from the setting of ambulance level and ward level of the ENT-clinic of Jena University Hospital.

In event that too few controls can be recruited from this setting for good comparability, study-related examinations are carried out on corresponding controls from Tinnitus Centre of the ENT- clinic of Jena University Hospital or on patients from dental practices established in Thuringia.

The study will be matched according to age and gender.

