## 4.5 Patient and subject recruitment

Both collectives will be recruited and examined by the same examiner.

Patients are recruited from the ENT-clinic of Jena University Hospital during EMG consultation hours on Tuesdays, within the framework of part-time inpatient facial nerve palsy training of Jena Facial Nerve Centre and patients with acute facial nerve palsy within the inpatient stay.

Recruitment of suitable controls also takes place in the ENT-clinic of Jena University Hospital. Controls will be included who are undergoing inpatient treatment but not due to facial nerve palsy. Suitable controls must also not have suffered facial nerve palsy in their past. Furthermore, an attempt will be made to recruit patients via the Tinnitus Centre at Jena University Hospital. Furthermore, patients can be recruited from dental practices established in Thuringia, if this is necessary for a better comparison result to the patient group.

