## 8.2 Data collection/documentation forms

Data collection necessary for the study will take place in the ENT-clinic of Jena University Hospital and, if necessary, in established dental practices in Thuringia. Data will primarily be collected in form of paper-based documentation forms and transferred to corresponding digital Excel spreadsheets.

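### Section 6.3 lets controls, but not patients, be examined in a dental practice; if this fallback is used, detection of the examiner-scored primary variables could differ by group

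*Protocol*

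**What the plan says.** Protocol section 6.3 makes three statements about the examination. On procedure: "Oral examination of patients follows the same procedure as that of controls". On place: "Examinations are carried out on premises of ENT department at Jena University Hospital". Then the exception: "An examination of controls is also conceivable in a dental practice". The exception names controls alone.

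Section 8.2 repeats the option. It locates data collection "in the ENT-clinic of Jena University Hospital and, if necessary, in established dental practices in Thuringia" and does not say for which group. Section 4.5 recruits patients only through ENT routes (EMG consultation, the facial palsy training, inpatient stays), so in practice the option concerns controls.

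The route is a fallback. Section 4.3 opens it "In event that too few controls can be recruited from this setting for good comparability". Examinations may then be done on controls from the tinnitus centre "or on patients from dental practices established in Thuringia", meaning a practice's own patients who serve as controls.

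Three safeguards are stated:
- Section 4.5: "Both collectives will be recruited and examined by the same examiner".
- Section 6.3 has the oral cavity inspected under good light.
- Section 3.1 says that controls are measured by the same methods as patients.

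The protocol does not say that chair, light source, drying or instruments are to be the same in both places. It sets no limit on the share of controls examined off site. Matching (4.3) is on age and gender only. The synopsis gives the number of study sites as one.

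**The concern.** The seven primary target variables in the synopsis (PSI, MPD, mod. SBI, PBI, PUFA, API, TI) are all scored by an examiner, by eye or with a probe. What an examiner finds can plausibly depend on light, positioning and drying. Plaque and bleeding indices are likely to be more sensitive to this than probing depth. If some controls are scored in a dental practice and every patient on ENT premises, measurement conditions are linked to group.

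Every patient-control comparison in section 6.7 (whole mouth, paretic side, non-paretic side) would carry that link. Better detection in the practice would make controls look worse and shrink a true patient deficit. Poorer detection there would exaggerate the deficit. Matching balances who is measured, not how, so it cannot correct this. Analysis can repair it only in part, because every participant examined in a practice would be a control.

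**Working it through.** **1. Reproduce the plan's own figure (section 7).** Inputs: Wilcoxon-Mann-Whitney, two-sided α = 0.05, d = 0.6666667, parent distribution min ARE (0.864), power 0.80, ratio 1. With n per group:

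- df = 2n × 0.864 − 2
- noncentrality = d × √(n/2 × 0.864)

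At n = 43, df = 72.3 and noncentrality = 0.6667 × √18.576 = 2.87, which gives power 0.809. This is the smallest n that reaches 0.80, so the stated 43 per group is confirmed. Going from 43 to 60 implies a drop-out allowance of 1 − 43/60 = 28.3%.

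**2. Model the setting effect.** Let f be the share of controls examined in a practice and b the shift in score due to setting, in SD units. The protocol gives neither, so both are assumptions shown over a range. The spurious group difference is

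bias ≈ f × b.

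Mixing two settings adds f(1 − f)b² to the control variance. At f = 0.5 and b = 0.3 this is 0.25 × 0.09 = 0.0225, which can be ignored.

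**3. Worked case: f = 50%, b = 0.3.**

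- Bias = 0.5 × 0.3 = 0.15 SD.
- Share of the planned effect = 0.15 / 0.6667 = 22.5%.
- If the bias opposes the true effect, the net effect is 0.6667 − 0.15 = 0.5167. At 43 per group the noncentrality is 0.5167 × 4.31 = 2.23, and power falls from 0.81 to 0.59.
- If there is no true difference and all 60 per group are analysed (normal-parent ARE 0.955), the noncentrality is 0.15 × √(30 × 0.955) = 0.80. The chance of a significant result is 0.125 instead of 0.05.

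**4. Range.**

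| f | b (SD) | bias (SD) | share of d | false-positive rate, 60 per group | power if opposed, 43 per group |
|---|---|---|---|---|---|
| 10% | 0.1 | 0.01 | 1.5% | 0.050 | 0.80 |
| 25% | 0.3 | 0.075 | 11% | 0.068 | 0.71 |
| 50% | 0.3 | 0.15 | 22.5% | 0.125 | 0.59 |
| 100% | 0.3 | 0.30 | 45% | 0.357 | 0.35 |

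The last row is a bound only, since section 4.3 looks first to the ENT clinic for controls.

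**5. What is not touched.** Section 6.7 also compares the paretic with the non-paretic side within a patient, and patients with each other. All patients come through ENT routes, so setting does not enter these comparisons. OHIP-G14, the secondary variable, is a questionnaire and is not scored by the examiner.

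**The case against.** The strongest case against the point is that the option may never be used. Sections 6.3 and 8.2 describe a possibility and a necessity clause, and 4.3 makes the practice route depend on a shortage of controls. One examiner sees both groups, with named indices, a stated common procedure and good light. A common procedure carried out in a different room is not in itself a contradiction. Nothing in the protocol describes the equipment in either place, so a difference in chair, light or drying is an inference. A sensitivity analysis by setting may stand in an analysis plan that is not shown, and the findings sheet, also not shown, may already record the place.

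Most of this stands and limits the point to a conditional one. It does not remove it. The protocol itself opens the unequal setting, and none of the safeguards fixes light source, drying or instruments across settings.

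A reader might infer three stronger things that the documents do not support:
- *That detection does differ by group.* This would need the option to be used and setting to have an effect; neither is established.
- *That poor yield on ENT premises lowers patient scores only.* ENT premises are the default for controls too, so it would lower the scores of ENT-examined controls as well.
- *That the patient deficit could be reversed.* Nothing in the protocol points to a setting effect of that size. Take an assumed finding with true prevalence 60% in patients and 40% in controls, detected with sensitivity 70% on ENT premises and 90% in a practice, and no false positives. The observed gap is 42% − 28% = 14 points with nobody off site, 42% − 32% = 10 with half the controls off site, and 42% − 36% = 6 with all of them. It shrinks but keeps its sign.

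**Conclusion.** The point holds in conditional form. Section 6.3 allows a measurement setting for controls that patients do not have, beside a promise of one procedure and a synopsis that lists one site. If the fallback is used, detection of the examiner-scored primary variables could differ by group, and the matching cannot correct it.

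The effect ranges from negligible (few controls off site, small shift) to material (half off site and 0.3 SD: a bias of 0.15 SD, 22.5% of the planned d). These sizes rest on assumed values of f and b and on treating the setting effect as a constant shift. The protocol supports no narrower range. No change to the sample size follows. This is a cheap improvement to make before off-site examinations begin, and not a defect in the within-patient or between-patient analyses.

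**What to change.** Amend sections 6.3 and 8.2 together, and reconcile them with the single site in the synopsis:

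1. Make ENT premises the setting for all participants where feasible, including controls recruited through a practice.
2. Where a control is examined in a practice, require the same examiner to use the same portable light, instruments and drying routine as on ENT premises.
3. Record the setting for each participant, if the findings sheet does not already do so.
4. Repeat the patient-control comparison without off-site controls, and say whether the matched patient is dropped with the control.

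Off-site controls will mostly be people attending a dentist. A change in the result in step 4 may therefore reflect who they are as well as where they were examined, and should be read that way.

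The cost is carrying a kit, or travel for a few controls who receive no compensation (section 10), and one further analysis on a smaller control group. With half of 60 controls excluded and all patients kept, the comparison is 60 against 30. That is equivalent to 2 × 60 × 30 / 90 = 40 per group, slightly below the 43 planned. Recruitment through practices can continue.

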| **Treatments/procedures, treatment plan (incl. follow-up)** | For controls and patients at one time:  - Informed study consent  - Completion of an initial questionnaire (questionnaire 1, subjective assessment of own oral hygiene and oral health)  - Oral health examination  - Completion of a second questionnaire (OHIP-G14 questionnaire on oral health-related quality of life)  - No treatment of patients and no follow-up care within the study, but within the individually annual dental check-up |
| **Schedule (study duration)** | Start: 01.05.2020  End: 30.12.2023  Patient-related:  Duration of study-related examination:  60 minutes |
| **Study sites** | n = 1 |
| **Statistical methods** | Descriptive statistics and interference statistics |
| **Funding** | Home remedies |

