## 4.2 Type of therapy assignment

No therapies will be performed on patients in sense of a study-related intervention. Routine dental examinations will be performed as indicated.

If desired, patients can receive expert advice for optimal oral care from the dentist during or after the examination and clarify open questions.

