## 6.4 OHIP-G14 questionnaire

After oral examination, the person is given another questionnaire to reflect the perceived oral health-related quality of life. Therefore the validated OHIP-G14 questionnaire is used. The person is asked to fill this out truthfully and intuitively as well. Alternatively, questionnaire will be discussed in interview.

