## 6.8 Tabular schedule

| 1. | information about the study and obtaining informed consent |
| --- | --- |
| 2. | handing out, answering and documentation of the 1st questionnaire  (Questionnaire 1, subjective assessment of own oral hygiene and oral health) |
| 3. | data collection during dental oral examination |
| 4. | documentation of data |
| 5. | handing out, answering and documentation of the 2nd questionnaire  (OHIP-G14 questionnaire on oral health-related quality of life) |
| 6. | analysis and evaluation of data |
| 7. | comparison of results |
| 8. | publication of results |

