# 9 Ethical considerations

Principles of "Declaration of Helsinki" (as of October 2013) are taken into account in planning of the study. No negative effects on patients and controls are to be expected as a result of the study. There is no risk for patients and controls. Treatment of patients will not be changed by the study. For participants, there is a one-time examination of 60 minutes due to the study.

Recommendations of "Good Clinical Practice", valid since 17.1.1997, will be taken into account, if applicable.

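### Oral-care advice and feedback of findings can reach participants before they complete the OHIP-G14, the secondary endpoint

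*Protocol*

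**What the plan says.** Four parts of the protocol bear on the order of events at the single appointment.

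- **Advice.** Section 4.2 states that, on request, "patients can receive expert advice for optimal oral care from the dentist during or after the examination". Section 6.3 repeats the offer without a time: "patients can ask the examiner open questions regarding oral care and receive expert advice for optimal tooth cleaning and plaque management".
- **Feedback of findings.** Section 6.3 says that the oral-health data of patients and controls "will be communicated to them and treated confidentially, but will have no influence on further dental and ENT treatment of patients". It gives no time for this.
- **OHIP-G14.** Section 6.4 fixes its place: "After oral examination, the person is given another questionnaire to reflect the perceived oral health-related quality of life". Section 6.4 also allows the questionnaire to be gone through in an interview. Section 3.2 makes it the secondary objective, to be compared with the control group and with palsy variables such as duration and cause.
- **Schedule.** Section 6.8 lists eight steps. The examination is step 3, documentation is step 4, and step 5 is "handing out, answering and documentation of the 2nd questionnaire", meaning the OHIP-G14. None of the eight steps is feedback or advice.

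**The concern.** The OHIP-G14 records how participants perceive the effect of their oral health on their lives. The examination looks at gum disease, untreated caries, plaque, the oral mucosa and halitosis. Someone who has just been told about such findings, or been advised on cleaning, may answer differently from someone who has not.

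Two features could make this uneven. Advice is given only to those who want it, so exposure differs from person to person. It is also worded for patients, while findings go to patients and controls, so exposure might differ by group. What is at stake is the patient-control comparison of the secondary endpoint and, within patients, its relation to palsy variables. Once a questionnaire has been answered after feedback, no later analysis can recover the answer that would have been given without it.

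**Working it through.** No figure in the protocol applies to this point, so the check sets the sections side by side.

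| Event | Where | Time the protocol gives |
|---|---|---|
| Questionnaire 1 (self-assessment) | 6.2; 6.8 step 2 | Before the examination |
| Oral examination | 6.3; 6.8 step 3 | Step 3 |
| Documentation | 6.8 step 4 | Step 4 |
| Advice, on request | 4.2; 6.3 | 4.2: from the examination onwards; 6.3: none; not a step in 6.8 |
| Communication of findings | 6.3 | None; not a step in 6.8 |
| OHIP-G14 | 6.4; 6.8 step 5 | After the examination |

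**Possible orders.**

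1. Advice during the examination falls in step 3 and so necessarily precedes the OHIP-G14 in step 5.
2. Advice after the examination may fall before or after step 5. The protocol does not choose.
3. Findings cannot be known before step 3, but may be communicated before or after step 5. Again the protocol does not choose.

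All three orders are allowed, and the first puts advice ahead of the questionnaire. Questionnaire 1 is also self-report, but its place before the examination protects it. The OHIP-G14 has no such protection.

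**Effect on the group comparison.** Let p be the share of a group that receives feedback or advice before the OHIP-G14, and s the mean shift in score among those who do, with subscripts P for patients and C for controls. The shift in the difference between group means is

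p_P × s_P − p_C × s_C.

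- If p_P = p_C and s_P = s_C, the shift is zero.
- If the shares or the effects differ, the shift is generally not zero.
- The protocol gives none of the four quantities, and s could have either sign: bad news and reassurance need not act the same way.

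The size therefore cannot be calculated from the document. Any percentage of false-positive results would rest wholly on an assumed shift, so none is given.

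**What is not affected.** The clinical indices listed as primary target variables are read by the examiner in step 3 and do not depend on what participants report afterwards. The sample-size inputs in section 7 do not involve the order of steps.

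**The case against.** The best case against the point is that unequal handling is not shown. Section 6.3 states that patients and controls are examined by the same procedure, section 4.5 has one examiner for both groups, and findings are communicated to both. The only sign of a difference is that the advice sentences speak of patients, and section 4.5 uses that word for prospective controls as well. This stands. The documents do not show that controls are denied advice or that the comparison is biased. It does not remove the gap in ordering, because advice on request still varies between individuals.

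A reader might also infer from the no-influence clause in section 6.3 that a finding needing care may not lead to care. The documents do not support that. The clause reads as the usual statement that an observational study does not alter care. Section 9 says much the same: "Treatment of patients will not be changed by the study". Usual-care routes are left open: the synopsis says "No treatment of patients and no follow-up care within the study, but within the individually annual dental check-up" and section 4.2 says "Routine dental examinations will be performed as indicated". Participants are told their findings, and nothing stops them acting on them. The information sheets, which are not shown, may say more. The remark in section 2.2 about prompt treatment of poor oral hygiene is background rationale and sets no study duty.

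Nor would it be right to say that advice has no stated time. Section 4.2 gives a window, and it is this window that lets advice precede the questionnaire. Only the communication of findings is untimed.

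**Conclusion.** The point holds as a narrow matter of ordering. As written, the protocol lets advice, and possibly feedback of findings, come before a self-reported secondary endpoint, with exposure that can differ between participants and possibly between groups. This follows from sections 4.2, 6.3, 6.4 and 6.8 alone.

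That answers would shift is plausible but not shown. A biased patient-control comparison needs the further assumption that exposure or its effect differs between the groups. Size and direction are unknown. The primary clinical indices and the sample size are untouched. It is a cheap improvement worth considering, not a flaw that undermines the study.

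**What to change.** State one order in three places:

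- **Section 4.2 and the advice sentence of 6.3:** *Once the OHIP-G14 is complete, patients and controls alike may, if they wish, receive advice on oral care.*
- **Section 6.3, communication of findings:** *Participants are told their findings only once the OHIP-G14 is complete.*
- **Section 6.8:** insert a step after step 5, *communication of findings and, on request, advice*, and renumber the later steps.

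Optionally, replace the no-influence clause in 6.3 with *No treatment is given within the study*, which matches the limits in the synopsis and in 4.2. This is for consistency only.

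The cost is a few short wording edits, with no extra visit or measurement. The drawback is that questions raised during the examination must wait until the OHIP-G14 has been answered, later in the same 60-minute appointment.
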